## Background

Obesity and its associated co-morbidities represent a global health threat causing 3.4 million preventable deaths annually. Bariatric surgery is the most effective treatment for patients with severe obesity producing sustained weight-loss with reduced morbidity and mortality. As a consequence of its unparalleled health benefits, bariatric surgery has been widely adopted with ~500,000 operations undertaken annually world-wide [1]. In the UK, patients with severe obesity, defined as a body mass index (BMI) of  $\geq 40$  kg/m^2, or  $\geq 35$  kg/m^2 with an obesity-associated co-morbidity, are eligible for bariatric surgery in accordance with National Institute for Health and Clinical Excellence (NICE) Guidelines [2].

## Variability in weight-loss response following bariatric surgery

Roux-en-Y gastric bypass (RYGB) and sleeve gastrectomy (SG) are the commonest bariatric procedures performed globally, accounting for 42% and 37% of operations undertaken in 2013 respectively [1]. Whilst at a population level these operations are highly effective at reducing weight it is now clear that, at the level of the individual, weight-loss following RYGB and SG is highly variable [3, 4]. Figure 1 shows the variability in 2-year percentage weight-loss (%WL) following RYGB and SG from our unit. Given the associated surgical risks, procedure cost and the need for lifelong nutritional monitoring there is an urgent unmet clinical need to improve weight-loss following bariatric surgery and improve the health of bariatric surgery patients.

**Figure 1: Weight-loss in patients who undergo sleeve gastrectomy or Roux-en-Y gastric bypass is highly variable**

[figure not shown]

The importance of maximising post-surgery weight-loss

Following RYGB and SG, glycaemic control improves rapidly by weight-loss independent mechanisms [5]. However, there is increasing evidence that long-term T2D remission depends on weight-loss [6-8]. In our patients, complete T2D remission rates at 2-years post-surgery (defined as HbA1c <6%, off all medication for more than 12 months) are determined by %WL, independent of procedure type (Figure 2). Importantly, multivariate logistic regression analysis correcting for confounding baseline factors shows that the odds of complete T2D remission increase by 10% for every additional 1%WL. Therefore, our data highlight the important clinical impact that small changes in %WL have on T2D remission, which has been shown to lead to a reduction in long-term microvascular disease outcomes [9]. Furthermore, the resolution and/or improvement of hypertension, dyslipidaemia, obstructive sleep apnoea and non-alcoholic steatohepatitis following bariatric surgery are positively associated with %WL [10-13] with weight regain leading to relapse of these co-morbidities [10, 11]. In addition, greater improvements in health-related quality-of-life (HRQoL) outcomes following bariatric surgery are reported with greater weight-loss [14, 15]. Taken together these findings represent a strong rationale for maximising weight-loss following bariatric surgery.

**Figure 2: Rate of remission of type 2 diabetes (T2D) following sleeve gastrectomy or Roux-en-Y gastric bypass is determined by weight-loss independent of procedure type**

[figure not shown]

Percentage of patients with T2D at the time of surgery in complete remission at 2 years after sleeve gastrectomy (n=118) or Roux-en-Y gastric bypass (n=116) plotted according to percent weight-loss category (<20%, 20-30% and >30%).

Rationale

Gut hormones levels in patients with poor weight-loss/ weight regain

The gastrointestinal tract is the body's largest endocrine organ, secreting a panoply of gut peptides in response to nutrient ingestion that play a key role in regulating energy and glucose homeostasis. Decreased caloric intake, due to reduced appetite, is the primary weight-loss driver following RYGB and SG in humans. The mechanisms underlying reduced post-surgery appetite remain to be fully elucidated, but post-operative changes in circulating gut hormones, in particular peptide YY (PYY), ghrelin and glucagon-like-peptide-1 (GLP-1) are key contenders [16, 17]. Indeed, cross-sectional studies show that patients with poor weight-loss post-RYGB exhibit increased appetite and caloric intake with higher acyl-ghrelin levels and lower GLP-1 and PYY circulating levels compared to patients with a good weight-loss response [18, 19].

The GLP-1 analogue liraglutide 3.0 mg reduces body weight and adiposity when administered daily subcutaneously to obese patients [20-24]. Importantly, a retrospective analysis of the effect of short-term (average duration 12 weeks) use of the synthetic GLP-1 analogue liraglutide in 15 patients with poor weight-loss following bariatric surgery found a significant reduction in %WL [21].

Our unpublished data show that patients with a poor weight-loss response (<20%) following SG and RYGB exhibit an attenuated post-surgery gut hormone response compared to patients with a good weight-loss response (>20%). In particular, we found that a proportion of patients with poor weight-loss exhibited a lower nutrient-stimulated GLP-1 response (delta active GLP-1 time 0 to time 30 minutes and active GLP-1 area under-the-curve) compared to patients with good weight-loss (Figure 3). This finding suggests that a pharmaceutical approach tailored to the patient's post-surgery gut hormone profile would improve %WL. Based upon these studies, an increment in active GLP-1 of less than 2-fold in the first 30 minutes following our standard meal test was identified as strongest predictor of poor %WL.

**Figure 3: Patients with poor weight-loss following RYGB and SG have an attenuated gut hormone response compared to patients with a good weight-loss response**

[figure not shown]

Patients with a poor weight-loss response (< 20%WL) following SG (n=10) and RYGB (n=10) and good response (%WL>20%) following SG (n=10) and RYGB (n=10) attended after an overnight fast for a 500 kcal test meal at time zero. Blood samples were collected at 15, 30, 60, 90, 120, 150 and 180 minutes post-meal. Active GLP-1 AUC in (A) SG patients and (B) RYGB patients and active GLP-1 fold-change from baseline at 30 minute post-meal in (C) SG and (D) RYGB were calculated for good and poor weight-loss responders. Acyl-ghrelin AUC in (E) SG and (F) RYGB and the fasted acylides-acyl ratio in (G) RYGB and (H) SG patients were calculated in good and poor responders. Data are mean  $\pm$  sem. \*  $p < 0.05$ , \*\*  $p < 0.01$ , \*\*\*  $p < 0.001$ .

---

## Hypothesis

Currently, there are no available pharmacological treatments for patients with poor weight loss after surgery and the only therapeutic option is revision surgery, which carries a mortality risk and is difficult to access. Based upon our data, we hypothesise that GLP-1 analogue administration to patients with poor weight-loss and a suboptimal GLP-1 response following RYGB or SG will lead to a greater reduction in body weight, adiposity and improvement in health and HRQoL outcomes compared to placebo.

## Objectives

To determine whether 24 weeks of subcutaneous liraglutide 3.0 mg causes greater %WL, reduction in adiposity and improvement in metabolic indices, physical function and HRQoL than placebo in patients with suboptimal nutrient-stimulated GLP-1 response and poor weight-loss following RYGB or SG.

## Primary objective

The primary objective of this trial is to compare the efficacy of 24 weeks of subcutaneous liraglutide 3.0 mg versus placebo administration, as an adjunct to diet and exercise, on %WL in participants with poor weight-loss and a sub-optimal active GLP-1 response following primary RYGB or SG at the end of the 24-week treatment period.

## Secondary objectives

To compare the effect of 24 weeks of subcutaneous liraglutide 3.0 mg versus placebo administration as an adjunct to diet and exercise in participants with poor weight-loss and a sub-optimal active GLP-1 response following primary RYGB or SG, at the end of the 24-week treatment period, upon:

1. Change in fat, lean body mass and bone density.
2. Change in circulating fasted glucose, insulin, HbA1c and leptin, and meal-stimulated glycaemic index, gut hormones and appetite response.
3. Change in HRQoL measures.
4. Change in physical functional assessments and activity levels.
5. Change in healthcare service usage.

## Trial design

This study is a double-blind, randomised, placebo-controlled, two-arm, parallel group, single-site trial (Figure 4). The purpose of this trial is to evaluate the therapeutic effects of liraglutide 3.0 mg in patients with 'poor' weight loss and a suboptimal glucagon-like peptide-1 response following bariatric surgery. The trial will test whether a 24-week administration of liraglutide 3.0 mg can improve weight loss in patients 1 year or more since primary RYGB or primary SG. Seventy participants will be enrolled to receive liraglutide 3.0 mg (n = 35) or placebo (n = 35) for 24 weeks. An identical placebo containing no active ingredients will be used as a comparator to evaluate the real treatment effect. Treatment allocation will be concealed from patients and investigators. A dose of 3.0 mg that is approved for weight loss will be used. This trial will test a longer treatment duration of 24 weeks as to extend the findings from a previous study that evaluated a treatment period of only 12 weeks [21]. Subject visits will be carried out at weeks 2, 4, 8, 17 and 24 of the treatment initiation. End-of-study visit will be over the phone 4 weeks after the end of treatment (i.e. week 28).

**Figure 4:** Flow chart of the BARI-OPTIMISE Trial

[figure not shown]

Abbreviation: BDI: Beck Depression Inventory, BIA: Bioelectrical Impedance Analysis, CSRI: Client Service Receipt Inventory (adapted), DXA: Dual Energy X-Ray Absorptiometry, EQ-5D: EuroQoL-5D, HRQoL: Health-

---

Related Quality of Life, IWQoL-Lite: Impact of Weight on Quality of Life-Lite, PA: Physical Activity, STS: Sit-to-stand, T2D: Type 2 Diabetes, 6MWT: 6-Minute Walk Test.

## Selection of Subjects

**Study population:** patients, 1 year or more following primary RYGB or primary SG, with poor weight-loss response (<20% WL) will be invited to participate. There will be no waivers to the inclusion and exclusion criteria.

### Inclusion criteria

1. Patients, 1 year or more since primary RYGB or primary SG, with poor weight-loss (<20% WL) that is not caused by either a surgical or psychological problem.
2. Adults, 18-64 years inclusive.
3. Suboptimal nutrient-stimulated GLP-1 response assessed by a meal test. Suboptimal active GLP-1 response is defined as a  $\leq 2$ -fold increase in active GLP-1 circulating levels between time 0 and time 30 minutes.
4. Females of childbearing potential and males must be willing to use highly effective method of contraception (Appendix 2) from the time consent is signed until 6 weeks after treatment discontinuation.
5. Females of childbearing potential must have a negative pregnancy test within 7 days prior to being registered for trial treatment. NOTE: Subjects are considered not of child bearing potential if they are surgically sterile (i.e. they have undergone a hysterectomy, bilateral tubal ligation, or bilateral oophorectomy) or they are postmenopausal.
6.  $\leq 5\%$  variation in body weight over preceding 3 months.
7. Fluent in English and able to understand and complete questionnaires.
8. Willing and able to provide written informed consent and comply with the trial protocol.

### Exclusion criteria

1. Had a surgical procedure other than gastric bypass and sleeve gastrectomy, or revision bariatric surgery of any operation type.
2. Pregnant or lactating mothers.
3. Participation in other clinical intervention trial.
4. Lifetime history of suicidal behaviour or severe depression assessed by direct questioning.
5. Clinically significant medical abnormalities (e.g., unstable hypertension, clinically significant ECG abnormalities, liver cirrhosis, AST or ALT  $> 3\times$  the upper normal limit).
6. Heart rate  $\geq 100$  beats/minute at screening on two separate measurements.
7. Uncontrolled hypertension (systolic blood pressure  $\geq 160$  mmHg or diastolic blood pressure  $\geq 100$  mmHg).
8. Renal impairment (estimated glomerular infiltration rate (eGFR  $< 30$  ml/min  $1.73\text{ m}^2$ )).
9. Known or suspected hypersensitivity to liraglutide 3.0 mg and placebo or any of the excipients involved in their formulation.
10. Personal or family history of medullary thyroid carcinoma or multiple endocrine neoplasia syndrome type 2.

- 
11. Personal history of pancreatitis.
  12. Uncontrolled hypothyroidism or hyperthyroidism.
  13. History of stroke, unstable angina, acute coronary syndrome, congestive heart failure New York Heart Association class III-IV within the preceding 12 months.
  14. History of arrhythmias.
  15. Inflammatory bowel disease.
  16. Diabetic gastroparesis.
  17. Concomitant GLP-1 receptor agonist usage.
  18. Concomitant usage of medications that cause weight gain or weight loss.
  19. Concomitant usage of DPPIV-inhibitors.
  20. Insulin usage.

## Recruitment

Participant recruitment will only commence when the trial has been confirmed by the Sponsor, issued a Trust Confirmation of Capacity and Capability and the trial site has received the Open to Recruitment Letter. The clinical bariatric teams at UCLH, the Homerton Hospital and the Whittington Hospital specialist bariatric centres (800 patients undergoing bariatric surgery per annum) will identify patients fulfilling the eligibility criteria. The Whittington Hospital will act as PIC and the trial will be undertaken at UCLH. Patients will be considered to be enrolled into the trial following: consent, baseline assessments, randomisation, allocation of the participant trial number and intervention.

## Study procedures and schedule of assessments

### Informed consent procedure

The person taking consent will be GCP trained, suitably qualified and experienced, and have been delegated this duty by the CI. At first, suitable patients will be identified by the bariatric team during their post-surgery follow-up visits at bariatric centre and asked if they are interested to take part in the study. Verbal consent will be sought from interested patients before they are approached by a research investigator who will explain the screening procedure as well as the aims, methods, anticipated benefits and potential hazards of the study. The investigator will also explain that patients are under no obligation to undergo screening and enter the trial and that they can withdraw at any time without having to give a reason. Those patients interested in taking part to the trial will be asked to sign a first consent form in order to undergo screening for this trial, as the assessment includes a meal test that is considered research procedure. Written informed consent will be sought within one week with a minimum of 24 hours after being approached and given the Participants Information Sheet (PIS). An original copy of the signed informed consent form will be given to the participant in addition to the original copy that will be filed in the Trial Master File (TMF). A copy will be placed in the medical notes. In addition, the consent process will be documented in the medical notes for a clear audit trail.

If a patient does not meet all the inclusion and exclusion criteria no further action will be taken and the patient will be informed that, for their own safety, it is not appropriate they continue with the study. Screening failure patients might be contacted for other research studies should they be interested.

---

A research investigator will notify patients of screening outcome via phone call. The investigator will explain again study aims, methods, anticipated benefits and potential hazards to qualifying patients and answer any questions they may have. Eligible patients will be asked to sign a second consent form, the study consent form, to confirm their willingness to take part to the trial. No study procedures will be conducted prior to the patient giving consent by signing the consent form. The investigator will also explain that patients are under no obligation to enter the trial and that they can withdraw at any time during the trial, without having to give a reason. Written informed consent will be sought within one week with a minimum of 24 hours after being approached and given the study PIS.

An original copy of the signed informed consent form will be given to the participant in addition to the original copy that will be filed in the Trial Master File (TMF). A copy will be placed in the medical notes. In addition, the consent process will be documented in the medical notes for a clear audit trail.

If new safety information results in significant changes in the risk/benefit assessment, the PIS and consent form will be reviewed and updated if necessary and subjects will be re-consented as appropriate. Therefore, the version and date of the PIS and ICF in use at the time will be recorded in the medical notes.

The investigator obtaining consent will register the participant for the study by entering all baseline data regarding the participant on the database. The system will then assign a unique participant identification number (PIN) to that participant that needs to be recorded on the consent form. No eligibility waivers or deviations will be permitted.

### Randomisation Procedures

Following participant screening, consent and baseline measure collection, the randomisation procedure will be remotely carried out by the Sealed Envelope, an independent specialised company that provides 24/7 cover to undertake the randomisation, and unblinding if required. The type of randomisation to be used is a stratified block randomisation with random block sizes. Subjects will be randomly assigned in a 1:1 ratio to receive either liraglutide 3.0 mg or placebo, stratified for type of surgical procedure and T2D status. This will be done by accessing the randomisation system website through the internet. The investigator will provide participant's initials, date of birth and stratification information before a randomisation code can be generated for each participant. Both participants and investigators will be blinded to study-group assignments. A randomisation notification message will be automatically generated to confirm the success of the randomisation process to the investigator, no group allocation will be disclosed. A randomisation notification email will be generated and sent to the pharmacist reporting the participant randomisation code; this randomisation code will reveal group allocation when identified in the code list. Only the trial coordinator and the trial pharmacist will have access to the code list. The blinding of the trial will be maintained throughout the trial until all data entry and processing are complete, the database has been locked and data analysis performed. Participants will be given a 24-hour Contact Card for emergency unblinding if required, medical support, or for any enquiries they have throughout the study period. For details on unblinding procedure refer to the trial Randomisation, Unblinding and Code break SOP.

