### Unblinding

---

The trial code will only be broken for valid medical or safety reasons e.g. in the case of a severe adverse event where it is necessary for the treating health care professional to know which treatment the participant is receiving before providing appropriate treatment. Subject always to clinical need, where possible, members of the research team will remain blinded. For details on unblinding procedure refer to the trial Randomisation, Unblinding and Code break SOP.

In the event a code is required to be unblinded a formal request for unblinding will be electronically submitted by the authorised investigator to Sealed Envelope using the online unblinding facility, available 24 hours daily. Alternatively, a request to the holder of the code break list, or their delegate, will be made and the unblinded information obtained. The pharmacist and the Trial Co-ordinator will be the solely holders of the code list, other than Sealed Envelope.

If a treating physician, who is not the CI/PI/trial investigator, requires the treatment to be unblinded in an emergency situation, they should notify the Investigating team that an emergency unblinding is required for a trial subject. The investigator/research team will provide this information as quickly as possible. On receipt of the treatment allocation details the CI/PI/trial investigator, or treating health care professional, will deal with the participant's medical emergency as appropriate.

The CI/PI will document the breaking of the code and the reasons for doing so on the CRF/data collection tool, in the site file and medical notes. It will also be documented at the end of the study in any final study report and/or statistical report. The CI/Investigating team will notify the JRO (acting on behalf of the Sponsor) in writing as soon as possible following the code break detailing the necessity of the code break.

The CI/PI will also notify the relevant authorities. The written information will be disseminated to the Data and Safety Monitoring Committee (DSMC) for review in accordance with the DSMC Charter.

Unblinding for the submission of SUSAR reports:

The following procedure will be used to unblind for the submission of a SUSAR report to the regulatory agencies:

- A member of the JRO Sponsor's office will contact the pharmacy requesting unblinding information from the randomisation list.
- The pharmacist will provide their email address and name for the request to be formalised in an email.

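### The trial coordinator holds the list that decodes treatment codes, with no separation of duties described: an avoidable risk to the blind

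*Combined protocol and SAP*

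**What the plan says.** Two sections of the protocol set the access rule. Randomisation Procedures: "Only the trial coordinator and the trial pharmacist will have access to the code list". Unblinding: "The pharmacist and the Trial Co-ordinator will be the solely holders of the code list, other than Sealed Envelope". The first also says what the list does: "this randomisation code will reveal group allocation when identified in the code list".

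The blind is stated in two places. Trial design: "Treatment allocation will be concealed from patients and investigators". Randomisation Procedures: "Both participants and investigators will be blinded to study-group assignments". That section also says blinding lasts until the data are entered and processed, the database is locked and the analysis is done. SAP section 3.3 likewise delays unmasking until after lock, SAP approval and replication of the primary analysis.

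On individual code breaks the Unblinding section adds: "Subject always to clinical need, where possible, members of the research team will remain blinded". For SUSAR reports, the sponsor's office asks pharmacy for the allocation, and the result is not passed to the trial team.

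**The concern.** A double-blind trial normally gives the decoding list only to people who have no part in running it day to day. The title of trial coordinator suggests someone close to daily conduct, and the protocol makes this person one of two local holders of the list.

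The trial has one site and leaves several matters to judgement. Persistent non-compliance can end in withdrawal (Assessment of compliance). Inconsistent data are checked with the researchers and may be set to missing (SAP 3.3). Missing week-24 weights may be imputed from self-reported weight (SAP 5.5). The primary analysis uses all available data as randomised (SAP 5.3). If knowledge of the arm reached whoever takes these decisions, retention or data handling could differ by arm and affect the primary comparison. If it reached participants or assessors, the questionnaires, appetite scores and effort-dependent physical tests would be the outcomes most open to influence.

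**Working it through.** No arithmetic applies. Who holds the list is not an input to the sample size (difference 5 %WL, SD 5.4%, 90% power, 5% significance, 20% drop-out) or to the SAP 5.3 model. The check is a comparison of the relevant statements.

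1. **Is the access real?** Yes. It is stated in both Randomisation Procedures and Unblinding, and the two agree. It is a written rule and not a gap in the text.

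2. **What does access allow?** Reading an allocation needs two things: the list and that participant's code. The coordinator has the list. On the code, the protocol says: "A randomisation notification email will be generated and sent to the pharmacist reporting the participant randomisation code". The coordinator is not named as a recipient. The code is not confined to pharmacy, though, because the sponsor's SUSAR request must quote the participant's PIN and randomisation code. A list holder could therefore plausibly decode some participants, but the documents do not show how many.

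3. **Who is stated to be blinded?** Patients or participants, and investigators. The coordinator is in neither group by name. The wider aim in Unblinding covers members of the research team, qualified by clinical need and by what is possible. The SUSAR procedure covers the trial team without that qualification. Whether the coordinator belongs to either team is not stated; the title makes it likely.

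4. **What is the coordinator's copy for?** Unblinding gives the list one use, as a second route for a code break: "Alternatively, a request to the holder of the code break list, or their delegate, will be made and the unblinded information obtained". The routes compare as follows:

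| Route | Needs the coordinator's copy? |
|---|---|
| Provider's online code break, open 24 hours | No |
| Request to a list holder or delegate | No, the pharmacist also holds the list |
| SUSAR unblinding | No, it goes to pharmacy |

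No described procedure depends on the coordinator. The mention of a delegate, which is not limited to pharmacy, also lets access extend beyond the two named roles.

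5. **Is any safeguard described?** The online route needs a formal electronic request from an authorised investigator, and a code break must be documented. Nothing similar is described for a holder who simply consults the list, and no separation of the coordinator's duties is given. Both sections refer to a Randomisation, Unblinding and Code break SOP, which is not among the documents.

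6. **Do the statements fit together?** Poorly. Withholding each SUSAR result from the trial team achieves little if a likely member of that team holds the key to the codes.

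**The case against.** The strongest reply is that the protocol may deliberately designate two unblinded roles. The stated blind covers participants and investigators, and the coordinator is called neither. The protocol gives consent, registration, entry of randomisation details, pre-visit contact, the end-of-trial call and documentation of non-compliance to the investigator. Data corrections go through a Data Manager and authorised staff. Nothing says that the coordinator recruits, assesses or handles data, and a firewall may be set out in the SOP or in the front pages, which were not available.

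Much of this stands, and it rules out four stronger readings that a reader might infer:

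- *The blind is broken.* Access is a risk. No disclosure is documented, and the coordinator is not among those expressly stated to be blinded.
- *The coordinator can read all 70 allocations.* That needs every participant's code, and the notification email goes to the pharmacist.
- *Coming allocations are exposed.* The list is described as decoding a code, not as showing the order of future assignments. Randomisation is remote, in blocks of random size, and no enrolment duty is given to the coordinator.
- *There is no operational need.* The list does have a stated use as the alternative code-break route, and only the provider is said to be available around the clock. A second local holder is back-up cover.

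The reply does not remove the access rule itself, the poor fit with the protocol's own aims, or the fact that the same cover is available without the coordinator.

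**Conclusion.** The point holds as an avoidable risk to the blind. The protocol gives the coordinator the decoding list, the available text describes no separation from recruitment, assessment, data queries or withdrawals, and the arrangement is inconsistent with the aims for the research team and for SUSAR results. The coordinator's copy is largely, though not wholly, redundant.

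No size can be attached: the documents give no basis for estimating either the chance of disclosure or the bias that would follow. The point is worth correcting but does not by itself call the results into question.

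This rests on two assumptions: that the coordinator belongs to the trial or research team, which is inferred from the title, and that the unseen SOP does not already impose a firewall. If the SOP does so, the remaining task is to state it in the protocol.

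**What to change.** In Randomisation Procedures and in Unblinding, limit the code list to the randomisation provider and the trial pharmacist. Specify that the delegate allowed for in the alternative code-break route is a pharmacy delegate, and bring the code-break SOP into line.

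The cost is a wording change in two sections and the SOP, and one fewer back-up contact for unblinding. The provider's 24-hour service and the pharmacist or delegate cover that loss. No design figure or analysis changes.

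If the sponsor has a reason to keep the coordinator as a holder, the weaker alternative is to state that this role is unblinded and to describe its separation from recruitment, assessment, data queries and withdrawal decisions, with a log of every look-up.

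If the coordinator has already had access, wording alone cannot undo it. The trial report should state the coordinator's duties, whether the list was consulted, and for which participants.
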